### Statistical Design and Analysis

The standard deviation used to calculate sample size is derived from results of the alpha phase. In order to have power of 0.9 to detect a difference of 5 mmHg with beta = 0.20 and alpha = 0.05, 337 patients would be required in each group.

Descriptive statistics will be calculated for all variables of interest. Continuous measures will be summarized using means and standard deviations whereas categorical measures were summarized using counts and percentages. For univariate analyses, two sample two-sided t tests will be using for continuous data, whereas chi-square analyses (or Fisher's exact tests in the case of cell sizes) will be used for categorical data. Regression analyses will be constructed from covariates known to impact on blood pressure. All analyses will be carried out using SAS Version 9.1 (SAS Institute, Cary, NC, USA).

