**Methods:**

This study will test the effect of a systems change on the management of high blood pressure in real world practice in primary care in Ontario, Canada. The systems change intervention involves an interprofessional educational program bringing together physicians, nurses and pharmacists with tools for both providers and patients to facilitate blood pressure management. Each of two waves of subjects were enrolled over a 6 month period with the initial enrollment between waves separated by 9 months. Blood pressure will be measured with the BpTru ^® ^automated blood pressure device. To determine the effectiveness of the intervention, a before and after analysis within all subjects will compare blood pressure at baseline to annual measurements for the three year study. To assess whether the intervention has an impact on blood pressure control independent of community trends, a betwen group comparison of baseline blood pressures in the delayed wave will be made with the immediate wave during the same time period, so that the immediate wave has experienced the intervention for at least 9 months. The total enrollment goal is 5,000 subjects. The practice locations include 10 Family Health Teams (FHTs) and 1 Community Health Centre (CHC) and approximately 49 primary care physicians, 15 nurse practitioners, 37 registered nurses and over 150 community pharmacists across the 11 communities throughout the province of Ontario. The 11 primary care sites will be divided into immediate and delayed groups based on geography and the use of an electronic versus a traditional chart patient record.

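### The sample-size sentence gives power 0.9 and beta 0.20 for the same test; the power attached to 337 per group is therefore either 0.90 or 0.80, and the article does not show which

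*Protocol article*

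**What the plan says.** The section Statistical Design and Analysis of the protocol article sets the sample size in two sentences. The first gives the source of the variability but no value: "The standard deviation used to calculate sample size is derived from results of the alpha phase". The second claims "power of 0.9 to detect a difference of 5 mmHg with beta = 0.20 and alpha = 0.05" and concludes that "337 patients would be required in each group".

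The sample-size sentence does not say whether the test is one- or two-sided. The next paragraph of the section does so for the analysis: "two sample two-sided t tests will be using for continuous data". The alpha-phase results, reported in the section on the High Blood Pressure AIM, are percentages only; no blood pressure SD appears there. The abstract (Methods) sets the recruitment target: "The total enrollment goal is 5,000 subjects". The article restates neither power nor beta anywhere else.

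**The concern.** Beta is the probability of missing the target difference and power is its complement. For one test, one difference, one alpha and one sample size, power 0.9 requires beta 0.10, and beta 0.20 requires power 0.80. The sentence asserts power 0.9 and beta 0.20 together, so one of them is an error.

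This is not a detail that a journal article may leave to a fuller document. It is a contradiction between two printed figures in intact prose, in the article's sole power statement. At stake is what the 337 promises: a 10% or a 20% risk of missing a 5 mmHg difference. Anyone citing the planned power of the between-group comparison would have to guess.

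**Working it through.** **Inputs from the article** (Statistical Design and Analysis): difference 5 mmHg; alpha 0.05; power 0.9; beta 0.20; 337 per group. Enrolment goal 5,000 (abstract, Methods).

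**Assumptions:** two equal groups, independent patients, normal approximation. Alpha is taken as two-sided, in line with the planned t tests; the one-sided case is shown as well.

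**Formula:** n per group = 2 × [(z for alpha + z for power) × SD / 5]². Solved for the SD: SD = 5 × √(n/2) / (z for alpha + z for power). With n = 337, the numerator is 5 × √168.5 = 64.90.

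**Step 1. Can 337 be reproduced?** Not from the article alone, because no SD is printed. The SD that 337 implies is:

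| Reading | Two-sided | One-sided |
|---|---|---|
| Power 0.90 (beta 0.10) | 64.90 / (1.960 + 1.282) = 20.0 | 64.90 / (1.645 + 1.282) = 22.2 |
| Power 0.80 (beta 0.20) | 64.90 / (1.960 + 0.842) = 23.2 | 64.90 / (1.645 + 0.842) = 26.1 |

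**Step 2. Whole-number SDs, two-sided.**
- SD 20, power 0.90: 2 × (3.2415 × 4)² = 336.2, rounded up to 337. The exact t calculation gives 338.
- SD 23, power 0.80: 333, close but not equal.
- SD 20, power 0.80: 2 × (2.8016 × 4)² = 251.2, rounded up to 252.

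SD 20 at power 0.90 is therefore the only whole-number two-sided match. One-sided, SD 22 at power 0.90 gives 332 and SD 26 at power 0.80 gives 335.

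**Step 3. How far apart are the readings?** At a given SD, the required n differs by the factor (3.2415 / 2.8016)² = 1.34.
- If the SD was 20: 337 per group for power 0.90, 252 for power 0.80.
- If the SD was about 23.2 (23.17 unrounded): 337 per group gives power 0.80, and power 0.90 needs 452.

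Power of 337 per group by assumed SD: 0.95 at 18, 0.90 at 20, 0.84 at 22, 0.81 at 23, 0.74 at 25.

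**Step 4. Set against planned enrolment.** The totals are 2 × 337 = 674 and, for power 0.90 at the larger SD, 2 × 452 = 904. The goal of 5,000 is 5,000 / 904 = 5.5 times the larger figure. With an assumed even split of 2,500 per group and SD 23.2, the standard error of the difference is 23.2 × √(2/2,500) = 0.66 mmHg if patients are independent. A 5 mmHg difference is then more than seven standard errors.

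**The case against.** The strongest reply is that the slip does no harm. Enrolment is planned at 5,000, not 674, so a 10% or 20% false-negative risk at 337 per group describes a sample at which the trial does not intend to stop. No enrolment figure or analysis in the article depends on which value is right. That largely stands, and it limits the weight of the point. It holds only when patients are counted as independent, however. The article assigns whole sites, 11 in all, and 337 carries no stated allowance for that. For illustration, take about 5,000 / 11 = 455 patients per site and 2,500 per group. The effective number per group, 2,500 / (1 + 454 × ICC), is about 451 at an assumed intraclass correlation (ICC) of 0.01, 248 at 0.02 and 105 at 0.05. The article gives no ICC, so these figures show only that the surplus cannot be taken at face value. Correcting the sentence does not resolve that question either way.

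A second reply is that the answer is obvious: SD 20 reproduces 337 at 90% power, so beta is a misprint for 0.10. This is plausible but not established. The value 20 comes from assuming 90% power, so it cannot then confirm it. The SD is also said to come from pilot data and need not be round: an SD of 23.15 at power 0.80 gives 2 × (2.8016 × 4.63)² = 336.5, which also rounds up to 337.

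A third reply is that an article may omit the SD. That is fair, and the omission is not the fault raised here. It matters only because it leaves the reader unable to resolve the contradiction.

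**Conclusion.** The contradiction is real and wrong as written: power 0.9 and beta 0.20 cannot describe the same test. The power attached to 337 per group is 0.90 or 0.80, a two-fold difference in false-negative risk and a factor of 1.34 in the required number at a given SD. The implied SDs of 20.0 and 23.2 mmHg rest on a two-sided alpha of 0.05, equal groups and independent patients; one-sided they are 22.2 and 26.1.

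A reader might infer two stronger things that the article does not support. One is that the power is undefined; it is ambiguous between two values, with some indication in favour of 0.90. The other is that the trial is underpowered. Nothing in this error shows that, since the enrolment goal is well above 674 or 904 on a patient-level count. The correction would make the stated power right; it would not establish the power of a comparison between 11 assigned sites.

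**What to change.** Retrieve the alpha-phase SD that was actually used, then restate the sentence with:

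- one consistent pair, either power 0.90 with beta 0.10 or power 0.80 with beta 0.20, whichever produced 337 with that SD;
- the SD itself, and whether alpha is one- or two-sided;
- a note that 337 per group is a patient-level figure with no stated allowance for assignment by site.

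An SD of 20 should not be inserted merely because it fits. The cost is one look-up in the pilot data and one rewritten sentence. The correction itself needs no extra patients and no change of design.

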## Methods and design

### Overview of the Evaluation Methodology

#### Evaluation Design

To evaluate this initiative, a prospective delayed intervention design has been selected. See Table 2 for key evaluation indicators. Although all sites ultimately will receive the intervention, six of the sites will be assigned to receive the intervention immediately (these sites will be referred to as "immediate intervention group"), while the remaining five sites will receive the intervention after several months, but will serve as a comparison during this delay period (these sites will be referred to as "delayed intervention group"). Further details regarding assignment to the immediate and delayed intervention groups will be discussed in a later section.

**Table 2 T2:** Key Evaluation Indicators of Interest

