##### Assignment to Immediate Intervention and Delayed intervention groups

Assignment to the immediate intervention and delayed intervention groups will be conducted at the site level rather than at the practitioner level or patient level. This is to mitigate the potential risk at a site of "contamination" of the comparison by practitioners sharing tools and information about hypertension management (as well as patients), if some practitioners at a site were assigned to the immediate intervention group and some to the delayed intervention group.

Initial consideration was given to randomizing the groups, however with only 11 sites, randomization posed risks of introducing bias. Sites in neighbouring communities could have cross contamination; the diverse and vast geography of the Province of Ontario must be accounted for, particularly because of the more rural north and the more densely populated south. Also, approximately half of the clinics had adopted an electronic medical record at study start, indicating the potential for the more rapid adoption of new techniques. With only 11 sites and too many variables to stratify by to allow randomization, in order to ensure that the sites in the immediate intervention and delayed intervention groups are not different from each other, the sites will be assigned to the intervention groups manually to ensure a distribution of the variables as evenly as possible. Allocation of sites into immediate intervention and delayed intervention groups will also take into consideration geographic proximity between sites. Sites in neighbouring communities will be allocated to the same grouping since communication between participants in proximal groupings could potentially contaminate comparisons.

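### For the immediate-versus-delayed comparison, the claim that 337 patients per group give power 0.9 for 5 mmHg does not fit the assignment of 11 whole sites

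*Protocol article*

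**What the plan says.** The sample-size statement is in the protocol article, Statistical Design and Analysis: "In order to have power of 0.9 to detect a difference of 5 mmHg", continuing "with beta = 0.20 and alpha = 0.05", and concluding that "337 patients would be required in each group". On the SD it says only this: "The standard deviation used to calculate sample size is derived from results of the alpha phase". The value is not printed. The section mentions no intracluster correlation, design effect or number of sites. For continuous outcomes it names a patient-level test: "two sample two-sided t tests will be using for continuous data". It also foresees regression on covariates.

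The design is set out elsewhere. Under Assignment to Immediate Intervention and Delayed intervention groups, assignment "will be conducted at the site level rather than at the practitioner level or patient level". Under Evaluation Design, "six of the sites will be assigned to receive the intervention immediately", and the other five form the delayed group. The Abstract (Methods) states "The total enrollment goal is 5,000 subjects" without linking that number to a power calculation. It gives two analyses: a before-after comparison within all subjects for effectiveness, and a comparison of the two waves over the same period to separate the effect from community trends.

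**The concern.** A figure per group with a stated power describes a two-group comparison, and here that is immediate against delayed sites. Patients at one site share clinicians, a record system and a workshop, so their blood pressures are likely to be correlated. The protocol's own reason for assigning whole sites is that practitioners at a site share tools and information. Under such assignment, precision depends on the number of sites as well as the number of patients, and a site-level test has only 11 − 2 = 9 degrees of freedom.

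If 337 per group was computed as though patients were independent, the printed power is too high for this comparison. A reader could then take a null between-group result as evidence of no effect when the comparison had little chance of showing 5 mmHg. The power being claimed is also unclear, because 0.9 and beta = 0.20 cannot both be right.

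**Working it through.** **Inputs from the protocol.** Difference 5 mmHg; alpha 0.05, two-sided; power 0.9, or 0.80 if beta = 0.20 is taken; 337 per group; 6 and 5 sites; 5,000 patients in total.

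**Assumptions.** SD back-solved; ICC 0.01 to 0.05; equal site sizes within a group; 5,000 split as 2,500 per group; comparison of means without covariate adjustment.

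**1. Reproducing 337.** The individual-level formula is n per group = 2 × SD² × (z₀.₉₇₅ + z_power)² / 5².
- SD 20, power 0.9: 2 × 400 × (1.960 + 1.282)² / 25 = 336.2, rounded up to 337.
- Solving for the SD at n = 337 gives 20.0 at power 0.9 and 23.2 at power 0.80.

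A round SD returns the printed figure exactly, with no room for inflation. Because the SD is unprinted, this is not conclusive: SD 15 needs 190 per group, and 190 × 1.77 is also about 337.

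**2. Standard error under site assignment.** With m₁ = n/6 and m₂ = n/5 patients per site,

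SE = SD × √{ [ICC + (1 − ICC)/m₁]/6 + [ICC + (1 − ICC)/m₂]/5 }.

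Power comes from the noncentral t with 9 df and noncentrality 5/SE. The detectable difference at 90% power is approximately (2.262 + 1.383) × SE.

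**3. Results at SD 20.**

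| ICC | SE, 337 per group | Power | SE, 2,500 per group | Power | Detectable difference, 2,500 per group |
|---|---|---|---|---|---|
| 0.01 | 1.95 | 0.63 | 1.34 | 0.91 | 4.9 mmHg |
| 0.02 | 2.29 | 0.49 | 1.80 | 0.70 | 6.6 mmHg |
| 0.05 | 3.10 | 0.30 | 2.76 | 0.37 | 10.1 mmHg |

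At ICC 0 and 337 per group, the SE is 1.54 and the 9-df test has power of about 0.82. The normal approximation, which ignores the small number of sites, gives 0.73, 0.59 and 0.36 at 337 per group for the three ICC values.

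**4. If 337 was computed at power 0.80 (SD 23.2).** Power at 337 per group is about 0.51, 0.39 and 0.24. With 5,000 patients it is about 0.82, 0.57 and 0.29. The pattern is the same against either target.

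**5. The ceiling set by 11 sites.** As patients per site grow without limit, SE tends to 20 × √[ICC × (1/6 + 1/5)]. Power 0.9 needs SE of at most about 5/3.645 = 1.37. So ICC can be at most about (1.37/20)² / 0.367 = 0.013 with unlimited patients, and about 0.011 with 5,000. The normal approximation puts these limits at about 0.016 and 0.014.

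**6. Unequal sites.** The combined physician and nurse-practitioner column of Table 5 runs from 1 to 16 per site, a coefficient of variation of about 0.8. If patient numbers follow clinician numbers, true power is below the equal-size figures.

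**The case against.** The strongest reply is that the trial plans far more than 337 per group. The goal of 5,000 is 5,000/674 = 7.4 times the stated requirement, and at ICC 0.01 it gives about 0.91. This stands. A reader might infer that the trial cannot reach 0.9, or that adding patients never helps once sites are assigned. The documents do not support that: they give no ICC, and at ICC 0.01 power rises from 0.63 to 0.91 between 337 and 2,500 per group. The ceiling blocks 0.9 only above an ICC of roughly 0.01.

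A reader might also infer that the calculation has been shown to omit clustering. That goes too far, since the SD is unprinted and a smaller SD with unreported inflation would fit. The exact match at SD 20, the absence of any clustering term and the patient-level tests make omission much the likelier explanation.

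Third, the before-after comparison within all subjects carries the effectiveness question and is less directly affected. This stands and limits the point to the between-group comparison. But that comparison is the protocol's safeguard against outside influences, and a requirement per group relates to it.

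Fourth, covariate regression and adjustment for baseline group differences could reduce the residual SD and ICC, so the figures at ICC 0.05 are conditional, not expected. Analysis detail may also sit in an analysis plan that is not shown. Neither reply supports the printed power statement, which gives no basis in sites or clustering.

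**Conclusion.** The point holds for the between-group comparison. As printed, 337 per group with power 0.9 for 5 mmHg does not fit assignment of 6 versus 5 sites. At the back-solved SD of 20, any positive ICC takes power at 337 per group below 0.9, and over ICC 0.01 to 0.05 it is about 0.63 down to 0.30. Planned enrolment does better, at about 0.91 down to 0.37, and keeps 0.9 only if the ICC is about 0.01 or less.

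The direction of the error at 337 per group is firm given that SD. Its size depends on an ICC that the documents do not give, and on equal site sizes, an even split and no covariate adjustment. The conflict between 0.9 and beta = 0.20 is plain on the page and needs no assumption.

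**What to change.** In Statistical Design and Analysis:

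- Print the SD taken from the alpha phase.
- Reconcile power 0.9 with beta = 0.20 and say which value produced 337.
- Replace the present claim with the power, or the detectable difference, for 6 versus 5 sites and about 5,000 patients. Show it over an ICC range of 0.01 to 0.05, with unequal site sizes and a t reference with 9 df.
- Say what informs the ICC. Alpha-phase or Time 1 data can help, with two cautions. The alpha phase had only about 296 patients, so its estimate would be imprecise. Time 1 readings used a sphygmomanometer and later ones the BpTRU, so the value may not carry over.
- Keep 337 only as the unadjusted individual-level figure.
- State that the calculation concerns the between-group comparison and not the before-after analysis.

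The cost is a recalculation and revised wording. No extra patients are needed, but the stated power becomes less favourable.

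### Whole sites are assigned, but the named between-group tests treat patients as independent, so p-values for immediate versus delayed will be too small and intervals too narrow

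*Protocol article*

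**What the plan says.** Under Assignment to Immediate Intervention and Delayed intervention groups, the protocol article states that allocation "will be conducted at the site level rather than at the practitioner level or patient level". The reason given is contamination between practitioners at one site. Under Evaluation Design, "six of the sites will be assigned to receive the intervention immediately", while "the remaining five sites will receive the intervention after several months". The abstract adds: "The total enrollment goal is 5,000 subjects".

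The controlled contrast is described in the abstract's Methods: a "comparison of baseline blood pressures in the delayed wave will be made with the immediate wave during the same time period". Its stated purpose is to separate the programme's effect from community trends.

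For the analysis, Statistical Design and Analysis names "two sample two-sided t tests will be using for continuous data, whereas chi-square analyses", with Fisher's exact test as the alternative for categorical data. It then mentions regression built from covariates that affect blood pressure. The article mentions no site term, random effect, generalised estimating equation, cluster-robust variance, design effect or site-level summary.

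**The concern.** The unit of assignment is the site, but the unit in the named tests is the patient. Patients at one site share clinicians, a record system, a community and, in this study, the same workshop and team. The article itself expects sites to differ: it cites the rural north against the denser south, and electronic against paper records, as reasons for allocating by hand. Any such variation adds to the variance of the difference between six sites and five. A patient-level standard error leaves almost all of it out.

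The immediate-versus-delayed contrast is the only analysis that can separate the programme from outside influences, so a wrong error rate there undermines the controlled evidence. The same tests would naturally be used for the baseline group comparisons, where statistical significance decides what later analyses take into account. Patient-level tests would flag routine site variation as imbalance, so the error also reaches the choice of adjustment.

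**Working it through.** **Inputs from the article.** 11 sites (6 versus 5); enrolment goal 5,000; stated sample size 337 per group; difference 5 mmHg; two-sided alpha 0.05.

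**Assumed, because the article gives no value.** SD 20 mmHg; ICC 0.005 to 0.05; equal-sized sites; every enrolled patient contributes to the contrast.

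**The plan's own figure.** For independent patients, n per group = 2 × (1.960 + 1.282)² × SD² / 5². With SD 20 and power 0.90 this is 2 × 10.51 × 400 / 25 = 336.2, which rounds up to 337. The SD is back-solved, so this is not a strict reproduction. (The same sentence of the article also gives beta = 0.20; at power 0.80 the figure would need an SD of about 23.2.) On the SD 20 reading, 337 contains no allowance for clustering.

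**Design effect and true error rate.** With m patients per site, DE = 1 + (m − 1) × ICC. The patient-level standard error is too small by a factor √DE, so the true two-sided error of the nominal 5% test is 2 × [1 − Φ(1.96/√DE)].

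- 5,000 patients: m = 5,000/11 = 454.5
- 337 per group: m = 674/11 = 61.3

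| ICC (assumed) | DE, 5,000 | True error, 5,000 | DE, 337 per group | True error, 337 per group |
|---|---|---|---|---|
| 0.005 | 3.27 | 28% | 1.30 | 9% |
| 0.01 | 5.54 | 41% | 1.60 | 12% |
| 0.02 | 10.07 | 54% | 2.21 | 19% |
| 0.05 | 23.68 | 69% | 4.01 | 33% |

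At ICC 0.001 with 5,000 patients, DE = 1 + 453.5 × 0.001 = 1.45 and the true error is about 10%.

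**Interval width at 5,000 patients.** The naive half-width is 1.96 × 20 × √(1/2,727 + 1/2,273) = 1.11 mmHg. A site-level analysis has 11 − 2 = 9 df and multiplier 2.262. Its half-width is 2.262 × 20 × √(1/2,727 + 1/2,273) × √DE:

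| ICC (assumed) | Site-level half-width (mmHg) | Ratio to naive |
|---|---|---|
| 0.005 | 2.32 | 2.1 |
| 0.01 | 3.02 | 2.7 |
| 0.02 | 4.08 | 3.7 |
| 0.05 | 6.25 | 5.6 |

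At ICC 0.02 the standard error alone is wrong by √10.07 = 3.2. The 9-df multiplier raises the ratio to 3.2 × 2.262/1.96, about 3.7.

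**Simulation check.** With 20,000 runs per setting and no true effect, the patient-level t test at 5,000 patients rejected in 27.6%, 40.7%, 53.9% and 68.7% of runs at ICC 0.005, 0.01, 0.02 and 0.05. A t test on the 11 site means rejected in 4.9% to 5.3%. At ICC 0 both tests rejected in about 5%, as they should.

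**The case against.** The strongest reply is that the t and chi-square tests are labelled univariate, that a regression follows, and that a condensed article may leave the form of that regression to an analysis plan not shown. It is true that the regression is not fully specified and that a site term could be added to it. But the article describes it only through covariates known to affect blood pressure, and a site term there would not repair the tests that are named. The point is that the stated tests do not match the stated unit of assignment, which is more than missing detail.

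Second, effectiveness is to be judged by a before-and-after analysis within all subjects. That stands as a limit on scope: the error rates above apply only to between-group comparisons.

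Third, the size rests on assumptions. This also stands. At 337 per group and ICC 0.001 the error is only about 5.7%. Unequal sites would generally make matters worse (the physician column of Table 5 runs from 1 to 16), while manual balancing could move the error either way. The percentages are illustrations over a range, but the direction is not in doubt unless the ICC is essentially zero.

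Fourth, a random site intercept cannot be fitted to a site characteristic that has one value per site. That is correct, and such variables need a plain site-level comparison.

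**Conclusion.** The concern holds, and the plan is wrong as written for every patient-level comparison of the immediate and delayed groups. At the 5,000 goal the nominal 5% test has a true error of roughly 28% to 69% for ICC 0.005 to 0.05, and valid intervals are about 2.1 to 5.6 times as wide as the naive ones. At 337 per group the error is about 9% to 33%. These figures assume equal-sized sites that vary at random, and the error rates at 5,000 also assume that all patients contribute. The millimetre widths further assume SD 20; the error rates and width ratios do not depend on the SD. Correcting the standard error does not address the lack of randomisation, which is a separate source of bias. This should be settled before any between-group result is reported.

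**What to change.** For every immediate-versus-delayed comparison of patient outcomes, replace the patient-level tests with a mixed model: linear for blood pressure, logistic for control to target. Include a random site intercept (clinician within site if wanted) and small-sample degrees of freedom such as Kenward-Roger, about 9. Name a t test on the 11 site means, or site proportions, as the simple check. Use the same approach for baseline patient comparisons. Compare one-value-per-site characteristics at site level only.

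The change is to protocol or SAP wording and needs no new data. SAS 9.1 already fits the linear mixed model; confirm that the installed version can fit the logistic one, and otherwise use the site-proportion test.

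The real cost is precision. With SD 20 and 9 df, power for 5 mmHg at ICC 0.01, 0.02 and 0.05 is about 91%, 70% and 37% with 5,000 patients, and about 62%, 49% and 30% with 337 per group. The sample-size paragraph should therefore state the SD and ICC it relies on, and what 11 sites can detect.

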After patient information is entered into the dataset, monthly and quarterly confidential practice audit reports will be available to all practitioners on the secure website linked to the web-based dataset. Moreover, the practitioner will be able to access the data set at anytime and generate ad hoc "drill-down" reports on his/her patients only. While the same practitioner can compare aggregate data from different sites, he/she cannot access the individual patient information of another physician. The web-based dataset will generate regular confidential practice reports based on the data submitted, for each participating physician and nurse practitioner, comparing the practice to that of other providers at the same site and to those of the other sites and participating healthcare providers. Reports are also generated at a site level for the other healthcare providers to access.

The web-based dataset will be hosted on a Personal Health Information Protection Act (PHIPA) compliant server provided by the dataset developer.

The patient will also be offered the patient toolkit, including the "Take the Pressure Off" patient book. This patient resource provides information and education on hypertension, its risk factors, lifestyle change information, and lists other resources. The Patient-Provider Agreement will be reviewed and completed, including the BP goal, the patient's selected lifestyle risk factor which (s)he wishes to focus on in the coming months/years and the patient's personal plan of action for this selected lifestyle risk factor. The Patient-Provider Agreement is incorporated into the "Take The Pressure Off". The BP goal and patient selected lifestyle risk factor is also documented in the HBP Registration (baseline) and Flow sheet (follow-up) data forms.

In order to assess the impact of the Hypertension Management Initiative on both healthcare provider practice patterns and patient blood pressure readings and control, it is necessary to compare data from the pre-program period to the program period. In order to assess any changes from before to after the intervention, a combination of chart reviews, for the pre-program period, and the web-based patient dataset, for the program period, will be used. Thus, data about the practice patterns of individual healthcare providers and their individual patients' blood pressure data will be used as their own comparators pre-intervention versus post-intervention.

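### The before-after effectiveness comparison is within patients, but the only univariate tests the plan names are for independent samples, so its standard errors would be too large as far as pairing goes

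*Protocol article*

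**What the plan says.** The Abstract (Methods) sets out two questions. For effectiveness, "a before and after analysis within all subjects will compare blood pressure at baseline to annual measurements for the three year study". To separate the intervention from community trends, a "comparison of baseline blood pressures in the delayed wave will be made with the immediate wave during the same time period".

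Under Implementation of Toolkit and Interventions, a second before-after contrast sets pre-program chart data against the program dataset. There, patients' "blood pressure data will be used as their own comparators pre-intervention versus post-intervention".

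Statistical Design and Analysis is the only section on methods. Among its univariate methods, it states that "two sample two-sided t tests will be using for continuous data". Categorical outcomes get a chi-square test or, depending on cell sizes, Fisher's exact test. The section then adds: "Regression analyses will be constructed from covariates known to impact on blood pressure". It does not say which test serves which question. No paired test, change score, repeated-measures or mixed model is named anywhere in the article.

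**The concern.** The first question and the chart-review contrast both use two or more readings on the same patient. The two-sample t test, the chi-square test and Fisher's exact test all assume independent observations. The t test's standard error leaves out the covariance between a patient's readings, and the chi-square and Fisher tests make the same omission for the proportion controlled to target.

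At stake are the confidence intervals and p values for the comparison by which the article says it will judge effectiveness. The article names tests and places no limit on their use, so this is a stated method that does not fit one of the stated questions. An analysis plan that followed the section literally would carry the mismatch forward.

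**Working it through.** **Inputs from the document.** Difference 5 mmHg; two-sided alpha 0.05; 337 patients in each group; 11 sites; enrolment goal 5,000. The standard deviation is said to come from the alpha phase but is not printed. The power statement reads "power of 0.9 to detect a difference of 5 mmHg with beta = 0.20 and alpha = 0.05". Power 0.9 and beta 0.20 contradict each other. That is a separate matter, but it means both powers must be tried below.

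**Assumptions.** Within-patient correlation rho of 0.3, 0.5 or 0.7; equal variance at both readings.

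**Step 1: the plan's own figure.** For two independent groups, n = 2 × [SD × (z_alpha + z_power) / 5]².

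- Power 0.90, SD 20: 2 × [20 × (1.960 + 1.282) / 5]² = 336.2, rounded up to 337.
- Power 0.80, SD 20: 252. Reaching 337 at this power would need an SD of about 23.2.

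So 337 fits a two-independent-group calculation at 90% power if the SD was 20. This SD is back-solved, so the figure is not truly reproduced. The formula contains no term for pairing.

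**Step 2: standard error with and without pairing.**

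- Unpaired: SD × sqrt(2/n)
- Paired: SD × sqrt(2(1 − rho)/n)
- Ratio: 1/sqrt(1 − rho), whatever the SD and n

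With SD 20 and n = 337 pairs, the unpaired value is 20 × sqrt(2/337) = 1.54 mmHg.

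| rho | Paired SE (mmHg) | Unpaired/paired | True type I error of the nominal 5% t test | Pairs for 90% power at 5 mmHg |
|---|---|---|---|---|
| 0.3 | 1.29 | 1.20 | 0.019 | 236 |
| 0.5 | 1.09 | 1.41 | 0.006 | 169 |
| 0.7 | 0.84 | 1.83 | 0.0004 | 101 |

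A simulation (4,000 runs per rho, 337 pairs, no true change) agreed: the unpaired t test rejected in 0.021, 0.005 and under 0.001 of runs. The chi-square test, assuming 30% controlled and rho on a latent normal scale, rejected in 0.027, 0.015 and 0.004.

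**Step 3: practical effect.** With SD 20, rho 0.5 and 337 pairs, power for 5 mmHg is 0.965 unpaired and 0.996 paired. At 5,000 patients the unpaired standard error is 20 × sqrt(2/5000) = 0.40 mmHg, against 0.40 × sqrt(0.5) = 0.28 mmHg paired. A 5 mmHg change is 5/0.40 = 12.5 standard errors even unpaired.

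**Step 4: sites.** Stable differences between sites cancel in a within-patient contrast, but differences between sites in the change over time do not. With equal sites the average is 5,000/11 = 454.5 patients. If ICC is the between-site correlation of change, true SE/two-sample SE = sqrt[(1 − rho)(1 + 453.5 × ICC)]. At rho 0.5 this is 0.71 for ICC 0 and 1.66 for an assumed ICC of 0.01. It equals 1 at an ICC of (1/(1 − rho) − 1)/453.5, which is about 0.001, 0.002 and 0.005 for rho 0.3, 0.5 and 0.7. The document gives no ICC, so these values only illustrate the direction.

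**The case against.** The strongest reply is that the section never assigns the two-sample test to the before-after analysis. The article has several comparisons of independent patients for which the test has the right form, clustering aside: delayed-wave baseline against immediate-wave follow-up, baseline and demographic comparisons between groups, and pre-program readings between groups. The sample size is also framed for two groups. On that reading the within-patient method is simply left to a fuller plan, and the regression might carry it.

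This reading is possible, but the text does not state it. The tests are given for continuous and categorical data without restriction, and the regression is described only by its covariates. The reply does confine the defect to the before-after analyses.

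A second reply also stands: ignoring positive within-patient correlation costs precision and does not create false positives, and at 5,000 patients the cost for a 5 mmHg change is small.

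Two stronger readings are tempting, and the document supports neither:

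- A reader might infer that a two-sample test sets everyone enrolled against whoever returned, so that losses to follow-up shift the estimate. The article states no analysis set. Run on patients with both readings, the two-sample test gives the same mean difference as the paired test, so any such shift would come from the analysis set and not from the test.
- A reader might infer that the reported precision will prove too optimistic because of site clustering. That depends on a site-by-time correlation that the article does not give.

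**Conclusion.** The mismatch is real and limited. The article makes effectiveness a within-patient comparison, and the univariate tests it names are for independent samples, with no within-patient structure stated for the regression. Pairing alone overstates the standard error by about 20%, 41% or 83% at an assumed rho of 0.3, 0.5 or 0.7, equivalent to discarding 30%, 50% or 70% of the information. The direction is conservative for any positive rho.

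The absolute figures in mmHg also rest on an SD of 20 inferred from the stated sample size. Near the enrolment goal, pairing alone would be unlikely to change a conclusion about a 5 mmHg difference. The opposing effect of site-by-time variation cannot be sized from the document, so the net error should not be given a sign or a number. This is a correction worth making because it is cheap and specific. It is not a defect that invalidates the study.

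**What to change.** In Statistical Design and Analysis, match each method to its question:

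- **Before-after blood pressure:** a paired analysis or, better for repeated annual readings, a repeated-measures mixed model with patient and site effects and visit as a fixed effect.
- **Before-after proportion controlled:** McNemar's test for a single pair of visits, or a GEE or mixed logistic model that accounts for repeated measures and site.
- **Independent groups (between-wave and baseline group comparisons):** keep the two-sample t, chi-square and Fisher tests for these.

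State whether the covariate regression includes the within-patient structure. The cost is a few sentences. The procedures are standard in the software already named, and each patient's unique identifier already links baseline to follow-up, so neither the design nor the data collection changes.
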